## **11. Subject Confidentiality**

To ensure that patient, physician, and other informant confidentiality is preserved, individual identifiers (such as name and medical record number) are stored in a single password protected system that is accessible to study research, analysis and IT staff only. This system is hosted on site at UPenn and is protected by a secure firewall. Once a participant is in this system, they will be given a unique study identification number (ID). For obtaining Pennsylvania Healthcare Cost Containment Council data (PHC4), the individual study IDs will be combined with SSN and name in order to be linked with state-based discharge data to ensure all hospitalizations are being captured for the primary outcome. Hospital discharge data received from PHC4 will be de-identified and not include PHI. For obtaining NJDOH state-based hospitalization data, NJDOH will send state-wide inpatient data from 2016-2020 with name, DOB, address, gender, race, and ethnicity. Our data analysts will match on these variables to the enrolled participants. For obtaining DE state-based hospitalization data, the investigators will provide study start and end dates for entire project and DE will send identifiable inpatient hospitalization data to the investigators for that time period and the investigators will link to individually enrolled patients. Please note that for assessing hospitalizations at Penn Medicine, inpatient data will be assessed using PennChart, including any CareEverywhere data that has been imported into PennChart from outside Penn Med hospitals and that is already a part of the patient’s PennChart record. Any other datasets and computer files that leave the firewall will be stripped of all identifiers and individuals will be referred to by their study ID. The study ID will also be used on all analytical files. Please see attached document (W2H.Summary.of.Data.Protections) for full database security details. The medication adherence device will provide adherence data from each participant. This information is transmitted via cellular signal without any subject identifiers.

### **11.1. Subject Privacy**

Privacy refers to the person’s desire to control access of others to themselves. Privacy concerns people, whereas confidentiality concerns data. Describe the strategies to protect privacy giving consideration to the following: The degree to which privacy can be expected in the proposed research and the safeguards that will be put into place to respect those boundaries. The methods used to identify and contact potential participants. The settings in which an individual will be interacting with an investigator. The privacy guidelines developed by relevant professions, professional associations and scholarly disciplines (e.g., psychiatry, genetic counseling, oral history, anthropology, psychology). At the time that UPenn study staff receives patient data, they will upload the patient data into the secure, web-based database (REDCap) and a study ID number will be generated for each patient. A link between the study ID number and the patient PHI will need to be maintained to ensure that the study staff can track recruitment

## Remote monitoring and behavioral economics in managing patients discharged from the hospital with heart failure: a randomized clinical trial

efforts to potential participants and to avoid contacting any patients who have previously declined to participate. To ensure that patient confidentiality is preserved, individual identifiers (such as name) are stored in a single password protected system that is accessible to study research, analysis and IT staff only. This system is hosted on site at UPenn and is protected by a secure firewall. Once a participant is in this system, they will be given a unique study ID number. Any datasets and computer files that leave the firewall will be stripped of all identifiers besides the study ID and individuals will be referred to by their study ID only. The study ID will also be used on all analytical files. REDCap is a secure web application for building and managing online surveys and databases. The institution installing REDCap will store all data captured in REDCap on its own servers. Therefore, all project data is stored and hosted at the local institution (UPenn) and no project data is ever transmitted at any time by REDCap from this institution to another institution or organization. Privacy of all study data will be maintained by restricting access to the identifiable information only to approved study staff who have received subject confidentiality and privacy training. Study coordinators will access patient contact information from the database to conduct recruitment phone calls. The study coordinator will review the consent script, which will include a description of the voluntary nature of participation, the study procedures, risks and potential benefits in detail. Participants will be told that all information will be kept strictly confidential, except as required by law. Subjects will be provided a copy of the consent document. All efforts will be made by study staff to ensure subject privacy. Enrollment will be conducted by the study coordinators who will enter patient information directly into the WTH platform once a participant has consented to participate. This database is hosted on a secure server as detailed in the subject confidentiality section. Study coordinators may have to contact patients in the intervention and their support partners during the course of the study and will use the WTH database to access contact information to facilitate this contact. If the rate of non-adherence to medication and to weighing-in, as recorded by the medication adherence device and scale, rises above a certain threshold, the study team may also contact the participants' managing physician. If a participants' weight rises above a certain threshold across a specific time period, the study team may contact the participants managing physician to notify them. This will be explained to the participant in the consent process and when the details of study participation are explained by the coordinator. PHI will not be shared with anyone outside the parameters of the study as detailed in the Consent/HIPAA process.

### 11.2. Data Disclosure

The following entities, aside from members of the research team, may receive PHI for this research study: AdhereTech; Qualcomm/Integron The Office of Human Research Protections and the University of Pennsylvania; federal and state agencies (for example, the National Institutes of Health, the NJDOH, and the Pennsylvania Healthcare Cost Containment Council, Delaware Health and Social Services); and, other domestic or foreign government bodies if required by law and/or necessary for oversight purposes. [name], statistician, has left the University of Pennsylvania and moved to New York University. She will act as an adviser on this project and only have access to de-identified data.

### 11.3. Data confidentiality

The following methods will be employed to protect patient PHI for this research study:

x Paper-based records will be kept in a secure location and only be accessible to personnel involved in the study.

Remote monitoring and behavioral economics in managing patients discharged from the hospital with heart failure: a randomized clinical trial

1127 x Computer-based files will only be made available to personnel involved in the study through the use of  
1128 access privileges and passwords.

1129 x Prior to access to any study-related information, personnel will be required to sign statements  
1130 agreeing to protect the security and confidentiality of identifiable information.

1131 x Wherever feasible, identifiers will be removed from study-related information. A Certificate of  
1132 Confidentiality will be obtained, because the research could place the subject at risk of criminal or civil  
1133 liability or cause damage to the subject's financial standing, employability, or liability.

1134 x A waiver of documentation of consent is being requested, because the only link between the subject  
1135 and the study would be the consent document and the primary risk is a breach of confidentiality. (This is  
1136 not an option for FDA-regulated research.)

1137 x Precautions are in place to ensure the data is secure by using passwords and encryption, because the  
1138 research involves web-based surveys.

## 1139 **12. Consent Process Overview**

1140 We are requesting a waiver of the requirement to document consent and HIPAA authorization with a  
1141 signature for participants enrolled into this study since we believe that the research presents no more  
1142 than minimal risk of harm to subjects and involves no procedures for which written consent is normally  
1143 required outside of the research context. [45 CFR 46.117(c)(2)] Participants will enroll in this study via a  
1144 remote recruitment process, and therefore, we will read the IRB-approved Consent/HIPAA script over  
1145 the phone to each participant and ask them to provide verbal consent and verbal HIPAA authorization  
1146 for use of their data in the study. After a patient provides verbal consent, the coordinator will select this  
1147 option on the Consent/HIPAA screen on the participants' profile that was created during enrollment on  
1148 the WTH platform for this study. A copy of the Consent/HIPAA document will be included in the device  
1149 packet provided to them by mail to the patients' home address.

### 1150 *12.1. Potential Study Risks*

1151 As this study does not involve any medical decision making and only observes the use of social  
1152 behavioral approaches to encouraging patients to use evidence-based treatments that their providers  
1153 have prescribed them following their CHF diagnosis, we consider this study to be minimal risk. The  
1154 primary risk would be from a breach of confidentiality involving electronic medical record reviews and  
1155 monitoring of medication adherence with a medication adherence device and monitoring of weights  
1156 from an electronic scale, which will be maintained on the WTH platform. This risk has been mitigated by  
1157 extensive privacy protection protocols, a highly secure data storage system, and a plan to remove  
1158 identifiers from the data wherever possible. In addition, all study personnel will be held to high  
1159 standards of upholding confidentiality and safeguarding patient privacy.

### 1160 *12.2. Potential Study Benefits*

1161 This study is to test a new approach to chronic disease management that combines remote monitoring  
1162 devices and behavioral economic engagement incentives to reduce rehospitalization rates among  
1163 patients with CHF. The immediate benefits of this study for participants may include improvement for

Remote monitoring and behavioral economics in managing patients discharged from the hospital with heart failure: a randomized clinical trial

management of CHF, which may lower their risk for future morbidity and death, improved quality of life, and reduced medical care costs. Patients will be randomized into either an intervention group that receives the medication adherence device and scale or a control group that receives usual care. The potential public health impact of a successful intervention to improve management of CHF is enormous and could reduce the number of deaths in the United States substantially each year. The benefits of this research to the participants studied, and to society at large, far surpass the minimal risks.

### *12.3. Alternatives to Participation*

Patients are free to decline participation in this study. If they decline to participate, they will receive no reduction in the usual care received from their health care providers for this condition.

### *12.4. Data and Safety Monitoring*

This study has been determined to present minimal risk to participants. However, we have established a Data Safety and Monitoring Board of experts in statistics and congestive heart failure to monitor adverse events that occur with study participants. Every 3 to 6 months, all readmissions information is pulled from the UPHS EMR and two residents independently adjudicate every hospitalization. If there is discordance between adjudications, our heart failure expert, [name], makes the final adjudication. These reports are presented to the DSMB (blinded by arm) so that they can then be assessed for safety. The DSMB report (blinded and de-identified) and DSMB assessments will be submitted to the IRB at the time of Continuing Review.

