
## Remote monitoring and behavioral economics in managing patients discharged from the hospital with heart failure: a randomized clinical trial

During the device setup process, the coordinator will also explain to the patient that study staff will be monitoring their weight to see if their weight rises above a clinically-significant threshold. The patient will be asked to step on the scale twice in order to confirm that the device is setup properly and to provide a baseline weight. The coordinator will also explain to the patient that their weight measurements will be sent to their managing physician via PennChart on a weekly basis. The coordinator will send a weekly report of weight measurements via Way to Health to the managing physicians in the patient reported flowsheet. Participants in the intervention will also be sent inspirational/motivational messages at random time points that encourage healthy behaviors for congestive heart failure. At the end of study participation, some participants will also be asked to complete an interview about their experience in the study. This project will consist of semi-structured telephone interviews with patients who participated in the intervention arm of the CHF Empower project. We will identify study participants who graduated from the program in the past four months and represented one of four categories noted in the table below. We will identify patients with high rates of adherence (90%) and low rates of adherence (or equal to 60%) as well as patients enrolled in the intervention group with any readmissions or no readmissions. Patients from each of the categories noted below will be targeted for interviews. We anticipate these numbers will double by the end of the study period as we recruit graduates prospectively. Research coordinators will conduct semi-structured telephone interviews with approximately 7-10 individuals from each group. Research coordinators will call the identified individuals and ask for verbal consent to a 45-60 minute interview. If unable to reach by phone, the coordinators will send them a letter with information on how to contact the study to complete the phone interview. Participants will receive a \$50 incentive for their participation in the interview. Attached is the interview script with themes to be discussed with interview participants as well as sample questions. The questions noted below are a guide; however, interviewers are expected to probe as appropriate. All interviews will be tape recorded, and ADA Transcription service will transcribe them. The Senior Qualitative Research Scientist will assist with initial coding and oversee the development of a codebook. Two research coordinators will code each of the interviews. Codes will be compared at the completion of each set of coding, and any disparities in coding will be discussed and adjudicated by the Research Scientist. In addition, at the end of study participation, some providers will also be asked to complete an interview about their experience in the study. Providers and staff dyads (a cardiologist and their nurse, for example) will be selected based on the number of weight gain alerts they received for their patients in 2019. Providers will be categorized by the number of alerts they received (total in 2019), and then the top 2 quartiles will be eligible for contact. Research coordinators will conduct semi-structured telephone interviews with approximately 15 physicians and 15 nurses. Providers will receive an email from the PI asking them to participate. Research coordinators will follow up to schedule interviews. The identified individuals will be asked for verbal consent to a 15-30 minute interview. The attached interview guide details themes to be discussed with interview participants (providers) as well as sample questions. The questions are a guide; however, interviewers are expected to probe as appropriate. Participants (providers) will be offered a \$25 Amazon gift card for their participation. All interviews will be tape recorded and ADA Transcription Service will transcribe them. The Senior Qualitative Research Scientist will assist with initial coding and oversee the development of a codebook. Two research coordinators will code each of the interviews. Codes will be compared at the completion of each set of coding, and any disparities in coding will be discussed and adjudicated by the Research Scientist.

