
Health to PennChart. Way to Health will push the abnormal weight measurement questionnaire responses to the managing physician in PennChart after the coordinator determines that a true weight increase has occurred. If the coordinator cannot reach the patient on the first phone call attempt, they will call the patient again on the following day. If the patient is unresponsive again, the coordinator will send a message to the patients managing physician through PennChart to inform them that the patient has an unconfirmed weight gain. Weight alerts will be monitored every day, including weekends and holidays. If a weight alert is produced on a weekend or holiday, the coordinator will call the patient to validate the weight increase with the abnormal weight measurement questionnaire, and if completed, will send the questionnaire responses to the patients managing physician through PennChart. Participants will also receive motivational/ inspirational messages on random dates throughout the 12 months. These messages are delivered automatically through the Way to Health platform via the participant's choice of communication (text, email, IVR). Additional extended non-adherence letters that will be sent to intervention patients and their providers at specified time points if a) they were never set up on their devices after multiple attempts to reach them by study staff or b) if they were using their devices and then stopped and study staff has been unable to reach them after multiple attempts. The patient letter for extended nonadherence will be sent at 2 weeks, 3 months and 6 months. The patient letter for never set up on devices will be sent out 4 weeks after non being able to reach patient. The provider letter for extended nonadherence will be sent after 3 weeks, 3 months and 6 months of being unable to reach the patient. The provider letter for never set up on devices will be sent out after 5 weeks of being unable to reach the patient. These additional attempts are being implemented because when intervention patients do not use their devices, we are unable to monitor their weights and medication adherence, and cannot route a result to their care teams that alert them of any clinically significant weight gains. At the end of study participation, participants will be made aware of their last date in the program and that they will no longer have to use the medication adherence device or the scale, and that research staff will not be monitoring their devices or reaching out to them as they have during their participation. Participants will be asked to complete a survey to provide feedback on their participation in the study. Patients randomized to the control group will be sent a hard copy of the informed consent and letter verifying enrollment with study contact information. For the qualitative interviews, Clinical Research Coordinators will contact selected participants and providers via telephone to request their participation in a semi-structured interview. Those participants who are not reached by phone will be sent a follow up letter with contact information for how to complete the phone interview. Providers will be sent an email to invite them to participate, followed up by a phone call. Consent will be requested on the phone, and after verbal consent is granted, the interview will begin. Interviews will take approximately 45-60 minutes for participants and 15-30 minutes for providers. Providers will receive an email from the PI asking them to participate. Research coordinators will follow up to schedule interviews with providers. Those identified individuals will be asked for verbal consent to a 15-30 minute interview. All interviews will be tape recorded, and ADA Transcription service will transcribe them. The Senior Qualitative Research Scientist will assist with initial coding and oversee the development of codebooks. Two research coordinators will code each of the interviews. Codes will be compared at the completion of each set of coding, and any disparities in coding will be discussed and adjudicated by the Research Scientist.

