1462     guidelines for study monitoring by the Board. The Project Manager, in consultation with the Principal  
1463     Investigators as needed, will prepare the agenda via PPT presentation to provide a study overview,  
1464     review recruitment methods, and proposed methods for the identification and reporting of adverse  
1465     events.

1466     Meetings of the DSMB will be held as conference calls as determined by the Chairperson. An emergency  
1467     meeting of the DSMB may be called at any time by the Chair, should participant safety questions or  
1468     other unanticipated problems arise. The open portion of the DSMB meetings are attended by the  
1469     Principal Investigators, key study personnel, and the DSMB members. The closed session is attended by  
1470     the project leader and the DSMB members.

1471                           12.4.1.4.4.     *Meeting Format*

1472     Since the study is open-label, DSMB meetings will consist of open sessions. Discussion held in all  
1473     sessions is confidential. The Principal Investigator and key members of the study team will attend.  
1474     Discussion will focus on the conduct and progress of the study, including participant accrual, protocol  
1475     compliance, and problems encountered.

1476     If necessary, an *executive session* will be attended by voting DSMB members. The executive session will  
1477     be held to identify and discuss the DSMB's recommendations. The study staff may be present, at the  
1478     request of the DSMB, during the executive session.

1479     Each meeting must include a recommendation to continue or to terminate the study made by a formal  
1480     DSMB majority or unanimous vote. Should the DSMB decide to issue a termination recommendation,  
1481     the full vote of the DSMB is required. In the event of a split vote, majority vote will rule and a minority  
1482     report should be appended. The DSMB Chair provides the tiebreaking vote in the event of a 50-50 split  
1483     vote.

1484     A recommendation to terminate the study may be made by the DSMB at any time by majority vote. The  
1485     Chair should provide such a recommendation immediately by telephone and email to the NIH Program  
1486     Official. After the NIH Program Official makes a decision about whether to accept or decline the DSMB  
1487     recommendation to terminate the study, the PI is immediately informed about his decision.

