Remote monitoring and behavioral economics in managing patients discharged from the hospital with heart failure: a randomized clinical trial

1623  
1624 A secondary endpoint will be cause-specific rehospitalization, the rationale being that evaluating cause-  
1625 specific hospital admission will allow a more complete understanding of the potential effects of the  
1626 intervention, by indicating how many of the readmissions are due to what cause (e.g., heart failure, MI,  
1627 stroke, other cardiovascular cause, non-cardiovascular cause, etc).  
1628

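### The plan does not mask those who assign cause of readmission, although the EMR they draw on holds intervention-only entries, and it has no rule for admissions known only from a state discharge record

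*Supplement*

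**What the plan says.** **The endpoint.** The final SAP (Data analysis plans) states: "A secondary endpoint will be cause-specific rehospitalization". It lists example categories such as heart failure, MI and stroke. Final protocol section 6 makes this a between-arm comparison of times to event.

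**The adjudication.** Section 12.4 of the final protocol says that every 3 to 6 months readmission records are drawn from the UPHS EMR and "two residents independently adjudicate every hospitalization". A heart failure expert decides where the two disagree. Sections 12.4.1.3 and 12.4.1.4 repeat the procedure.

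**What is blinded.** The only masking statement attached to this process concerns the output: "These reports are presented to the DSMB (blinded by arm) so that they can then be assessed for safety". Section 12.4.1.4.4 (Meeting Format) gives the trial's status: "Since the study is open-label, DSMB meetings will consist of open sessions".

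**What the EMR holds for one arm only.** Under section 7.2 the coordinator will "send a weekly report of weight measurements via Way to Health to the managing physicians in the patient reported flowsheet". Section 7.2 also has staff send a PennChart note to the clinician on the fifth day of non-adherence. Section 9.2 adds that "Way to Health will push the abnormal weight measurement questionnaire" responses to the physician's PennChart once a gain is confirmed, and that a PennChart message is sent when a gain cannot be confirmed.

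**Admissions outside UPHS.** Section 10 adds discharge data from Pennsylvania, New Jersey and Delaware. Section 11 adds CareEverywhere records already imported into PennChart. On the Pennsylvania file it says: "Hospital discharge data received from PHC4 will be de-identified and not include PHI".

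**The concern.** Deciding whether an admission was for heart failure takes judgement, and borderline cases can go either way. A Way to Health weight-gain entry shortly before admission tells the reader two things. It identifies an intervention patient, and it suggests fluid overload, since the protocol's own background section treats weight gain as an early sign of decompensation. A run of stable recorded weights would point away from heart failure, again for intervention patients only. Control patients have no equivalent entries. The same clinical picture could therefore be labelled differently in the two arms.

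Heart failure readmission is the cause that this intervention targets most directly, so readers will give that secondary result weight. Differential labelling could create an apparent effect on it or hide a real one.

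A second, smaller gap concerns admissions found only in state discharge data. The plan names no procedure for giving them a cause.

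**Working it through.** The plan gives no figure for misclassification, so there is none to reproduce. The check is a reading of the text, followed by an illustration of size on assumed inputs.

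**Step 1: does the text mask the adjudicators?** Sections 12.4, 12.4.1.3 and 12.4.1.4 each describe the residents and the expert. In all three, arm-blinding describes the reports given to the DSMB. Nothing says that the residents or the expert are masked, or that they work from redacted records.

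**Step 2: could the source reveal the arm?** Four kinds of PennChart entry arise only in the intervention arm: weekly weights, weight-gain questionnaires, unconfirmed-gain messages and non-adherence notes. The enrollment note is different. It records active participation, is not restricted to one arm and is not said to name the arm.

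**Step 3: does this adjudication define the endpoint?** Neither the final SAP nor protocol sections 6 and 10 say who assigns cause, or from which records. The link comes from the changes log. The Mod41 entry says CareEverywhere records are reviewed so that clinical reasons for outside readmissions are assessed by the procedures used for Penn readmissions. The resident adjudication is the only such procedure described.

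**Step 4: which admissions fall outside it?** CareEverywhere covers only what was already imported into PennChart. An admission seen solely in a state file has no stated route to a cause.

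**Step 5: how large could the distortion be?** Every input here is an assumption, and the true rate ratio is set to 1.

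*Model A, ambiguous admissions.* Of all admissions, 40% are truly heart failure. A definite fraction d is always called heart failure. An ambiguous fraction a is called heart failure with probability p_I (intervention) or p_C (control).

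Apparent ratio = (d + a·p_I) / (d + a·p_C)

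- a = 0.15, d = 0.325, 60% against 40%: (0.325 + 0.09)/(0.325 + 0.06) = 0.415/0.385 = 1.08
- a = 0.20, d = 0.30, 70% against 30%: (0.30 + 0.14)/(0.30 + 0.06) = 0.44/0.36 = 1.22

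*Model B, sensitivity gap.* The heart failure share is s, the false-positive probability is 0.05 in both arms, and control sensitivity is 0.90.

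Apparent ratio = [s·sens_I + (1−s)·0.05] / [s·0.90 + (1−s)·0.05]

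| s | sens_I = 0.90 | sens_I = 0.80 | sens_I = 0.70 |
|---|---|---|---|
| 0.3 | 1.00 | 0.275/0.305 = 0.902 | 0.245/0.305 = 0.803 |
| 0.4 | 1.00 | 0.350/0.390 = 0.897 | 0.310/0.390 = 0.795 |
| 0.5 | 1.00 | 0.425/0.475 = 0.895 | 0.375/0.475 = 0.789 |

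A labelling gap of 10 to 40 percentage points, depending on the model, moves a null ratio to between 0.79 and 1.22. The documents do not show whether any gap exists.

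**The case against.** The other side has several good points.

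- **Silence is not absence.** The protocol says readmission information is pulled and then adjudicated. It does not say that the residents browse outpatient flowsheets or in-basket messages. A reader might infer that the chart shows the arm, or that the adjudicators are known to be unmasked. The documents support neither as fact. They support that masking is unstated and that arm-revealing entries exist in the source system. This stands as a limit on the wording, but it does not close the gap.
- **Sources are not confined to UPHS.** Read alone, section 12.4 might suggest that cause comes only from UPHS records. Sections 10 and 11 contradict that, and the Mod41 log entry aims at the same procedure for outside admissions. This stands. What is left is the subset known only from state data, whose size is not given. De-identified return of the Pennsylvania file is not itself an obstacle to matching, because study IDs are submitted with the request for linkage.
- **The adjudication is described for safety review.** This also stands. But if another method was meant to define the endpoint, it appears nowhere, and the SAP still needs the text.
- **Safeguards exist.** Two independent readers and an expert tie-breaker reduce random error. They do not remove a bias that all three share by seeing the same entries.
- **The magnitudes are assumed.** This is true. They should not be set against the planned hazard ratio of 0.73, which is an all-cause figure.
- **The endpoint is secondary, added later, and has a partly descriptive rationale.** This limits severity. Section 6 nevertheless specifies a comparison between arms.

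**Conclusion.** The point holds in a limited form. The plan states no masking for the residents or the heart failure expert, in an open-label trial whose EMR holds entries that only intervention patients generate. If their adjudication supplies the cause-specific endpoint, the between-arm comparison is open to differential misclassification. That condition rests on the changes log, not on the SAP. The illustrative ratios show that a moderate gap could matter. They are not estimates, and the bias could run either way.

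A reader might extend the worry to the main result. That would be wrong: the primary outcome is readmission for any cause, and mislabelling the cause does not change whether an admission counts.

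The missing rule for admissions known only from a state record is a separate gap in specification, of unknown extent. Both matters deserve correction before the cause-specific results are interpreted. Neither threatens the trial's primary conclusion.

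**What to change.** 1. State in the SAP that the adjudicated causes define the cause-specific endpoint, who assigns them and from which sources.
2. Give the residents and the expert an admission packet (admission note, discharge summary, test results) without Way to Health flowsheets, weight alerts or study notes, and state that they are masked to arm.
3. Add a sensitivity analysis that defines cause for every admission, from every source, by principal discharge diagnosis. This also covers admissions known only from a state record. It assumes that the state files carry that field, which the documents do not confirm.

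Item 3 makes the sources uniform. It does not by itself remove bias, because treating clinicians who knew the arm may have influenced the discharge diagnosis. It belongs beside masked adjudication and does not replace it.

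The cost is a filtered export by the analysts who already pull the admissions, slightly longer packet preparation and one further analysis. No additional assessor is needed. Discharge codes are coarser than adjudication, so the two sets of results will not match exactly.
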